### Health-economic evaluation

A health economic evaluation in form of a cost-effectiveness analysis (CEA) and a cost-utility analysis (CUA) will be conducted resulting in an incremental cost-effectiveness ratio (ICER) and an incremental cost-utility ratio (ICUR), respectively. The effect parameter employed in the CEA is the primary outcome of the trial. Thus, the ICER will inform about the additional costs of an additional family with at least one parent who experienced a reduction in anxiety and depressive symptoms (assessed by a reduction at the HADS response by 1.6) during the intervention period from T0 to T2. The ICUR will be additional costs per improvement in parents’ quality-adjusted life years (QALYs) in a family, given as an equally weighted sum of QALYs of all parents, during the intervention period from T0 to T2. QALYs are based on the EQ-5D-5L [19] and evaluated by a German tariff [20] to generate utilities. The health economic evaluation will be conducted from the perspective of the SHI and the society.

The effect parameter and the EQ-5D-5L values are taken from the trial. Intervention costs (family-SCOUT salaries and travel costs) derive from the study documentation. Costs regarding physician contacts, hospital stays, medication intake, domestic help, inpatient care, and absent days are received from SHI data during the intervention phase (T0 to T2). In order to account for a societal perspective in the health economic evaluation, additional information is collected via questionnaires at T0 and T2, i.e., absent days as well as out-of-pocket costs induced at physician contacts, therapist contacts, domestic help, and rehabilitation. Indirect costs due to absent days will be evaluated by the human capital approach [21]. Moreover, we will consider family spillover effects as suggested for health economic evaluations with externalities [22, 23] by including health care costs of children which we receive also from SHI data. In particular, spillover effects are introduced based on the approach suggested by Al-Janabi et al. (2016) [24]. Costs and QALYs will not be discounted due to the short intervention period.

The statistical analysis of the health economic evaluation will follow the intention-to-treat approach. Multiple imputations to account for missing data will be conducted by considering the hierarchical structure of the data (regions and families). In sensitivity analysis, a full-case analysis will be conducted only with those families with complete data. The ICER and ICUR will be calculated based on the respective outcomes and costs of parents within the family (sum of costs induced by all parents of each family) whereas children’s costs are considered as a spillover effect. As health care use might be substantially higher previous to death and the intervention is not intended to have an effect on mortality, in sensitivity analysis, we will rerun the statistical analysis without families that experienced the death of a parent during the intervention phase. The non-parametric bootstrap method will be employed to generate 95% confidence intervals [25, 26]. In order to account for uncertainty, results will be presented on the cost-effectiveness plane and as a cost-effectiveness acceptability curve [27–30].

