#### Permanent contact person/family-SCOUT

The family-SCOUT provides a continuous contact throughout the entire course of disease including palliative situations, dying, death, and bereavement depending on the family’s need. Professionals working as family-SCOUTs have different backgrounds such as social workers or nurses with additional qualifications in psychotherapy. Additional training involves communicative skills, training in psycho-oncology, developmental psychology, and social law (80 h). The main tasks of the family-SCOUTs are related to all topics covering the family’s concerns, e.g., difficulties in organizing child care, needs for household support, self-assessment of communication behavior in the family, and ways of coping. The family-SCOUTs provide information about all options available for organizational, emotional, and communicative purposes and facilitate access to existing support services, e.g., domestic help, youth welfare services, cancer counseling services, and psycho-oncological services either face-to-face or by telephone. The family-SCOUTs also foster open discussions about the disease between parents and subsequently all family members and provide appropriate brochures and recommendations for reading materials designed for children.

Periods of intervention depend on the affected family’s needs; the observation time within the study is at least 9 months. In palliative situations and in the case of death, companionship by the family-SCOUT continues until stable everyday structures have become re-established and necessary support (e.g., psychotherapeutic support) can be securely offered within a stable framework. If single parents with an unfavorable prognosis are in need, support is provided for arranging a custody declaration in the case of death.

Through the outreach program of the Center for Integrated Oncology (CIO) Aachen-Bonn-Cologne-Duesseldorf (CIO^ABCD^), the family-SCOUT initiative will be closely connected regionally with oncologists in the inpatient and outpatient sectors, social services in the local hospitals, psycho-oncologists, youth welfare staff, pediatric psychotherapists, pediatric psychiatrists, and medical/psychological psychotherapists with training in family therapy.

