#### Specific family-centered and child-centered therapeutic interventions

When reaching their limits in open discussions with the families, the family-SCOUTs may involve specially trained therapists working on the basis of the COSIP (Children of Somatically Ill Parents) manual [12]. They will reinforce the parents’ skills, promote open discussion within the family, and support the children in coping with the given scenario by taking development-psychological aspects into account in an age-appropriate fashion. The setting may involve parental sessions, family sessions, and children sessions. No prior ICD diagnosis is required to receive the sessions fostering the preventive approach of the family-SCOUT concept.

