#### Statutory health insurance data

Statutory health insurance (SHI) data will be analyzed for all study participants who provided consent and are insured by one of the participating insurance providers. The data include master data, diagnostic data, and treatment data (type of treatment, with the date and costs) of outpatient care by physicians, in-patient care in hospitals, drugs and medication, rehabilitation, reintegration, domestic help, inability to work, domestic nursing care, and nursing services. SHI data covers the time period 12 months before intervention to the complete intervention time. Survey data will be linked with SHI data at the individual level for each respondent who has given consent for data linkage.

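### The stated intervention cost is narrower than the intervention described, and the economic comparison of non-randomised groups names no confounder adjustment for costs or QALYs

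*Protocol article*

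**What the plan says.** **Costing.** The section Health-economic evaluation states: "Intervention costs (family-SCOUT salaries and travel costs) derive from the study documentation". For other resources it states: "Costs regarding physician contacts, hospital stays, medication intake, domestic help, inpatient care, and absent days are received from SHI data". For the societal perspective, questionnaires at T0 and T2 add "absent days as well as out-of-pocket costs induced at physician contacts, therapist contacts, domestic help, and rehabilitation". Results are to be given from the insurer's and society's perspectives.

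**What the intervention contains.** Among the components under Description of the intervention, the article says that "the family-SCOUTs may involve specially trained therapists working on the basis of the COSIP (Children of Somatically Ill Parents) manual". Sessions may be held with parents, families or children. On access it says: "No prior ICD diagnosis is required to receive the sessions fostering the preventive approach of the family-SCOUT concept". The scouts themselves receive 80 hours of additional training.

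**Comparison of groups.** The effect measure of the cost-effectiveness analysis is the trial's primary outcome, and "The ICER and ICUR will be calculated based on the respective outcomes and costs of parents within the family". The statistical part of the economic section names intention to treat, multiple imputation respecting regions and families, a complete-data sensitivity analysis, another without families in which a parent died, and bootstrap intervals. On the insurance data, the article says: "SHI data covers the time period 12 months before intervention to the complete intervention time".

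**The concern.** The article says that the results will help decide whether statutory insurance should cover the service. For that purpose the cost must be that of the whole package under test. A component that only the intervention group receives, and that is missing from the cost definition, makes the service look cheaper than it is in both ratios.

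The second matter is comparability. The groups are not randomised, and the article itself lists this as a possible source of bias. For the clinical outcomes it plans confounder-adjusted regressions. For costs and QALYs it names none, although case mix at enrolment can affect both and 12 months of earlier insurance data are to be obtained.

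**Working it through.** **1. Is there a figure to reproduce?** The article gives no unit cost, ICER or ICUR. The only planning figures used here are the response rates in the section Sample size, and these reproduce. Exact power of Fisher's test (two-sided 5% assumed) is 91.7% for 28% versus 16% with 330 and 230 families (stated 90%). It is 86.0% for 30% versus 16% with 211 and 147 (stated 85%). The reduced sizes follow from 330 × 0.8 × 0.8 = 211.2 and 230 × 0.8 × 0.8 = 147.2. The planned differences are therefore 0.28 − 0.16 = 0.12 and 0.30 − 0.16 = 0.14.

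**2. Where could a therapist session be costed?**
- *Intervention costs:* scout salaries and travel. The therapists are people whom the scouts call in, so these two items do not evidently cover them.
- *Insurance cost items in the economic section:* no therapist item.
- *The fuller list in Statutory health insurance data:* outpatient care by physicians, hospital, drugs, rehabilitation, reintegration, domestic help, inability to work and nursing. Again there is no therapist item.
- *Questionnaires:* therapist contacts appear, but only as families' out-of-pocket cost, and only for the societal perspective.

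**3. Effect on the ratios.** ICER = ΔC / ΔE. If a cost c per intervention family is left out of ΔC, the ICER is too low by c / ΔE.
- At ΔE = 0.12: 100 / 0.12 = EUR 833 per additional responder family for each EUR 100 omitted.
- At ΔE = 0.14: 100 / 0.14 = EUR 714.
- Over an assumed range of c from EUR 50 to EUR 1,000, at ΔE = 0.12: 50 / 0.12 = EUR 417 to 1,000 / 0.12 = EUR 8,333.

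The ICUR shifts in the same direction by c divided by the QALY difference. No QALY difference is given, so that shift cannot be computed.

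**4. Is adjustment named anywhere for the economic quantities?**
- *Allocation:* Aachen contributes 265 families to the intervention group only and Düsseldorf 160 to the control group only. Bonn contributes 70 controls first and 65 intervention families later. Group is thus largely tied to region and, in Bonn, to period.
- *Effect:* the primary analysis of the primary outcome is an unadjusted Fisher test. An adjusted model for the same response is planned, but as a secondary analysis.
- *Targets of the adjusted regressions in Statistical methods:* HADS response and subscores, distress, fear of progression, parenting concerns, family functioning and KIDSCREEN. Costs, EQ-5D and QALYs are not on the list.
- *Insurance variables:* to be described and compared with adjustment for family clusters only.
- *Economic section:* imputation deals with missing values and the bootstrap with sampling error. Excluding families with a death conditions on an event after enrolment. None of these balances the groups at baseline.

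**5. How much could confounding matter?** The article gives no basis for an estimate. As an illustration only, with an assumed incremental cost of EUR 1,000, let confounding move ΔE over an assumed range of 0.06 to 0.15. The ICER then runs from 1,000 / 0.06 = EUR 16,667 down to 1,000 / 0.15 = EUR 6,667.

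**The case against.** The strongest reply is that this is a condensed article. The covariates of a cost model commonly stand in the full protocol or analysis plan, and nothing here says that the cost comparison is unadjusted. The adjusted secondary model covers HADS response, which is the effect measure. This stands to the extent that a reader may not infer an unadjusted comparison as fact. What remains is that the article itemises its adjusted targets without costs or QALYs, and says how insurance variables are compared, with family clustering as the only adjustment.

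On costing, the project shares its name with the scouts, so the salary item might include therapists paid by the project. The article does not say so. Its cost definition is explicit rather than silent, so condensation does not explain the mismatch.

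Several stronger readings are tempting and unsupported:
- *That the sessions are counted nowhere, or cannot appear in claims.* Waiving a prior diagnosis is a rule of access and says nothing about billing. The out-of-pocket share is recorded.
- *That scout training is omitted.* The 80 hours may be paid time within salaries, or set-up cost excluded by choice.
- *That the groups differ in disease stage, or that cost differences mainly reflect case mix.* The article says only that parents may enter at different stages, and reports no imbalance between groups.

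The analysis without families in which a parent died is also a partial safeguard against high end-of-life costs. It does not cover severely ill parents who survive to T2.

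**Conclusion.** The costing point stands. The stated cost definition is narrower than the intervention, and following it understates incremental cost in favour of the intervention in both ICER and ICUR. This assumes that sessions take place and that neither scout salaries nor the listed insurance items include them. The size is unknown, since the sessions are optional and neither their number nor their price is given. The EUR 833 per EUR 100 omitted is a conversion rate at the planned 12-point difference, not an estimate of the error.

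The adjustment point stands in a smaller form: no confounder adjustment is named for costs or QALYs, and the ICER is tied to an outcome whose primary analysis is unadjusted. A reader might infer that both ratios are biased by confounding. The document supports only a risk of that, of unknown direction and size.

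**What to change.** - Add therapist sessions delivered under the intervention to the intervention costs, with a named documentation source for their number and unit cost. State whether the 80 hours of scout training are contained in salaries.
- Estimate incremental costs, response and QALYs by regression within each bootstrap sample. Adjust for insurance cost in the 12 months before the intervention, EQ-5D utility at T0, and the sociodemographic and disease-specific covariates already planned for the clinical models. Compute the ICER and ICUR from these adjusted differences.

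The regression uses data that the project already plans to collect. The cost is some extra analysis work, a record of the sessions (the article does not say that one exists), and a somewhat less favourable ICER from the fuller costing. Adjustment will not remove unmeasured regional differences, since only Bonn supplies families to both groups. That limit should be stated with the result.

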### Qualitative data analysis

Qualitative content analysis of the transcripts will be carried out [18]. Triangulation of the resulting codes and categories with the standardized questionnaire data will take place on the basis of a mixed-methods matrix [31]. This allows personal and family-related qualitative and quantitative characteristics to be linked in order to identify and contrast-specific typologies or patterns that can be attributed to the intervention.

### Study monitoring

The intervention and data collection will be accompanied by continuous study monitoring and a formative implementation evaluation. The monitoring activity will ensure that the standardized training of the family-SCOUTs at both intervention sites and the intervention is in accordance with the study manual and that documentation is uniform and complete. Any divergences from the manual will be documented and adopted to later implementation strategies and potential revisions of the manual. In addition, the consent process of family-SCOUT is also quality assured at all sites through monitoring activities; the same applies to the data transmission routes in the evaluators’ data management. Monitoring will comprise regular phone calls, semi-structured interviews, and audits. It will cover compliance with the study protocol, compliance with the manual, observance of the inclusion criteria, completeness of documentation, unexpected events, and patient dropouts. Due to the noninvasive and need-oriented nature of the intervention, no termination criteria will be initially defined. However, unexpected events and their potential consequences for the families or staff will be documented and discussed at regular project meetings.

In addition, the numbers of enrolled patients and other organizational data are monitored and sent weekly to the consortium leader (RWTH Aachen University) and evaluators (CHSR Bonn). The study progress is reported quarterly and discussed with the whole consortium according to an approved milestone plan; for the oversight of data management, a group consisting of members of the evaluators and consortium leader was also established. All events, progress data, milestones, and failures are reported quarterly to the funding agency.

## Discussion

Parental cancer can put a strain on the whole family and often disrupts daily routines. Families with underage children often experience organizational and emotional limits and fail to organize essential support for themselves. Available services are insufficiently frequented and many social services end with the death of the affected parent. Underestimating the impact on all family members and psycho-social and emotional strains can lead to severe health problems and an increased rate of psychological complications in the later course. This problem is addressed by family-SCOUT, whose innovative concept offers affected families and their children a novel kind of support. A family-SCOUT is a steady contact person who advises, accompanies, and supports families according to their needs. Together they develop individual solutions beyond the limits of sectoral care. Supporting a family in which one of the parents has developed cancer is a complex challenge. With its outreach, cross-sector, and cross-phase concept that offer organizational, emotional, and communicative support, family-SCOUT aims to reduce stress and prevent secondary mental illnesses.

For the reasons outlined above, the hospitals’ psycho-social services staff are not adequately prepared for such complex interventions, and interventions that start too early are often unsuccessful [2]. A characteristic of the presented intervention in contrast to existing services is the “active outreach approach” with the aim to minimize barriers to support access. It is expected that through family-SCOUT, families can overcome some of the challenges they face after a cancer diagnosis is given to one of the parents. The characteristics of family-SCOUT, especially the low-threshold access, reduce barriers for families to take up the service, increases a broad acceptance amongst families, and reach families who previously had no access to support services. Currently poorly developed inter-sectoral links between the different service providers involved often lead to uncoordinated and structurally insufficient care for the families. This phenomenon is further accentuated by the heterogeneity of care structures involved as well as the fact that they are mostly based on local initiatives with variable goals [8]. It is therefore necessary to evaluate and establish approaches for comprehensive, structured care for families with minor children and parental cancer approaches that also can be flexibly adapted to the individual needs of all family members. Therefore, the concept of family-SCOUT is designed to meet the specific needs of the families and offers an entire range of support; ranging from support regarding social and financial issues, to application support for domestic help, or promotion of disease management among parents and children. Most existing support services are severely restricted in time and manpower and consequently, their provided service is unstable, non-continuous, and often restricted to the treatment of the affected cancer patient within a respective institution. Consequently, psychological burdens on the children that develop and/or manifest themselves later in the course of the disease or years thereafter are neither registered nor treated [8]. The innovative intervention approach of family-SCOUT is capable of relieving existing structural deficiencies for affected families and providing timely, needs-adjusted access to adequate support in a structured way. It can be assumed that this will be able to reduce the number of psychological sequelae and the associated healthcare costs for all members of the family.

### Limitations and generalizability

The study design is non-randomized and non-blinded. This might cause a bias between IG and CG, which could affect the main effect of the primary outcome. Differences in distributions of baseline variables between IG and CG will be discussed carefully. Some families that meet the inclusion criteria will not be included due to missing informed consent. Reasons for initial non-response will be documented. There might represent a selection bias in terms of greater enrolment of families who have time and resources to participate, although the outreaching time-flexible concept tries to counteract this. As the primary research data is based on a self-completion questionnaire survey, there might be a selection bias in terms of higher educated families with sufficient German language skills or without migration history. Families from the CG might be more likely to drop out than families from the intervention group, as a greater benefit can be expected there. At the time of inclusion, the affected parents may be at different stages of the disease. Patients may have been diagnosed with cancer only recently, and others may be post-recurrence, while another group may be in a palliative situation. Estimated effects and costs in the subpopulation with SHI data might be biased from this selection. In addition, the study recruits participants at four locations within Germany, which are located in immediate proximity, limiting the external validity. Caution should be applied with respect to generalizing the results.

### Trial status

Recruitment of participants for the study commenced in October 2018, and the first family was included on October 9, 2018. On September 29, 2020, 406 families have been assigned, 216 into IG and 190 to CG; currently, 45 families have participated in the semi-structured interviews. The estimated enrollment period, including recruitment and inclusion, is anticipated to be 27 months (December 31, 2020) and will conclude, when the estimated sample size has been included. The version number and date of the protocol are v1.0 and July 6, 2018, respectively.

